## Methods

### Research aim

The aim of this research is to assess the safety (evaluated as rate of hypoglycemia) that this 4-step strategy has on patients with T1D after completing a series of simulated soccer tests. As exploratory analysis, we will compare the performance of the skills required to achieve a good score in the selected test. We will also aim to identify an optimal pre-exercise blood glucose level associated with a better performance in simulated soccer tests. Finally, we will evaluate the effect of this 4-step strategy for blood glucose level control in the cognitive performance (indexed by neuropsychological evaluations testing executive functions, attention, working memory, psychomotor speed, and visual-spatial short-term memory) in patients diagnosed with T1D.

### Trial design

This is a randomized, crossover, double-blinded (subject and evaluator), controlled trial. Participants will be randomized to the order of the interventions assigned (real 4-step method versus usual recommendations (sham 4-step method)), leaving a washout period of 3 weeks for repeating assessments after switching groups. We follow the standard protocol items: recommendation for interventional trials (SPIRIT) guidelines to cover all sections involved in this protocol (see Additional file 1).

### Participants

Eligibility criteria for this trial will be focused on selecting patients with T1D that have a stable insulin regimen and glucose control and are engaged regularly in exercise and physical activities, as this is the target population to whom we would like to generalize the results obtained. Table 1 lists the inclusion and exclusion criteria for this trial. Participants are required to be able to understand instructions for motor and cognitive evaluations and to provide informed consent, in order to be enrolled.

**Table 1 Tab1:** Inclusion and exclusion criteria

Inclusion criteria	Exclusion criteria
Participants older than 18 years More than 2 years of established T1D Stable insulin regimen in the past 6 months indexed by less than 20% change in total insulin daily dose HbA1c less than 9.0% Weekly physical activity of 90 min or more Participation in recreational or competitive soccer-related activities, at least four times per month Participants able to provide informed consent	Any treatment regimen different from continuous subcutaneous insulin infusion or multiple daily insulin injections Any use of medications (other than insulin) known to affect glycemic control including oral or parenteral steroids (except for inhaled steroids), metformin, SGLT2 inhibitors, GLP.1 agonists, thiazolidinedione, sulfonylureas, DPP-4 inhibitors, or any other oral antidiabetic therapy Detectable C-peptide in serum Cognitive impairment comprising any substantial decrease in alertness, language reception, or attention that might interfere with understanding instructions for motor and cognitive testing, not including hypoglycemia unawareness Chronic kidney disease (glomerular filtration rate less than 90 mL · min^-1^) Chronic liver failure (Child-Pugh B or C) Advanced diabetic retinopathy Pregnancy Color blindness

*T1D* type 1 diabetes, *SGLT-2* sodium glucose cotransporter 2, *GLP1* glucagon like peptide 1, *DPP-4* dipeptidyl peptidase 4

### Recruitment

Recruitment of participants will be based mainly on referral by endocrinologists, internal medicine physicians or other professionals involved in the care of patients with T1D. However, we are also seeking to recruit patients in collaboration with members of the Diabetes and Endocrinology Medical Association in Costa Rica (ANPEDEM) and through the monthly meetings of the People with Diabetes National Foundation in Costa Rica (Dia Vida Foundation) and social media advertisements. Additionally, Institutional Review Board (IRB)-approved flyers with the trial information will be situated near the lobby of clinics and hospitals where patients with T1D attend for monitoring.

The trial research assistant will contact candidates through personal or telephone interview and will complete a pre-screening evaluation (see Table 3) form assessing all of the inclusion and exclusion criteria. Participants that fulfill the eligibility criteria will be defined as potential participants of the clinical trial, and will receive the informed consent form by mail or email. Afterwards, a face-to-face meeting will be scheduled and during this session (visit 1), the principal investigator will explain the methodology and the design of the study in detail. The subject will also be asked to give their written informed consent during this visit, after they have asked questions and/or expressed their concerns.

### Baseline assessments

Baseline assessments will be carried out by a physician and will take place after consent has been obtained and before randomization. During this visit (visit 1), a physician will complete an evaluation with clinical data about the subject’s physical activity routine, chronic diabetes mellitus control, history of hypoglycemia, and body mass index (BMI) measurement. Additionally, the following laboratory evaluations will be performed: fasting plasma glucose, serum C-peptide level, HbA1c and urinary albumin excretion in a spot urine sample. Following all baseline assessments the subject will be randomized to their respective arm.

One week after randomization, a second visit (visit 2) will take place during which a certified physical education teacher and a soccer trainer will give the participants a theoretical and practical explanation of the training session exercises that will be conducted in the trial. During this visit, the participants will execute a short version of the simulated soccer exercises to become familiar with them. Additionally, participants will receive an educational session with an endocrinologist with all of the indications to complete the blood glucose management through insulin and dietary adjustments.

### Intervention

The intervention will consist of either following the recently published ADA usual recommendations of care [12–16] before, during and after exercise (sham 4-step method), or the real 4-step method (a meal 60 min pre-exercise, with 50% of insulin dose; a low GI meal 60 min post-exercise, with 50% of insulin dose; a low GI snack at bedtime before sleep, omitting the insulin dose; and 20% reduction in the basal insulin dose). On the day after exercise, participants will return to their usual full basal insulin dose. Moreover, the type of insulin used in the clinical trial will not differ from that used by the participants prior to enrolling in the study. The ADA guidelines suggest that short-acting insulin is reduced depending on the mean exercise intensity in both exercise modes [16].

There will be specific evaluation of the intermittent modality of exercise, given that the main objective that guides this exercise protocol is not to demonstrate differences in the response of subjects with T1D to diverse exercise modalities, such as continuous versus intermittent exercise. On the contrary, the intervention will evaluate the impact in terms of the safety and performance of a protocol that sets forth insulin dosage along with carbohydrate intake diet modifications, compared with usual-care recommendations stated by guidelines for the standard of care. It is worth adding that other trials have evaluated the response of subjects to the 4-step method [2, 14, 15] in protocols that had evaluated continuous physical activity.

#### Active intervention: real 4-step method

Participants will come to the laboratory at 7:00 a.m. and we will first obtain a resting, fasted venous blood sample (via venipuncture) for the laboratory evaluations previously listed. The iPro2 Professional continuous glucose monitor (CGM) with Enlite sensor (Medtronic, MN, USA) will be installed at that time. Participants will then consume a standardized cereal-based breakfast meal (sugar-coated corn flakes, peaches, and semi-skimmed milk; 1.3 g carbohydrate · kg^-1^ body mass). At 1:00 p.m. participants will consume a standardized pasta-based lunch meal (pasta, tomato-based sauce, cheddar cheese, olive oil; 1.3 g carbohydrate · kg^-1^ body mass). Between the morning and evening visits, participants will record their self-measured glucose control every 2 h.

At 5:00 p.m. participants will arrive for the evening training session. Before starting this session, they will self-administer a 50% reduced pre-meal rapid-acting insulin dose into the abdomen (the injection site will be at the mid-point between the iliac crest and the navel). Immediately after receiving this insulin dose, participants will consume a pre-exercise carbohydrate bolus (sugar-coated corn flakes, peaches and semi-skimmed milk; 1.0 g carbohydrate · kg^-1^ body mass). Following this bolus, participants will remain rested for 60 min, at which point a finger stick sample for glucose testing will be drawn immediately before starting with the training sessions.

At 60 min post-exercise, participants will self-administer a pre-meal rapid-acting insulin dose reduced by 50%, into the abdominal site contralateral to the previously administered pre-exercise rapid-acting insulin injection. After receiving this insulin dose, participants will consume a carbohydrate-based meal (basmati rice, tomato-based sauce, turkey breast, and an isomaltulose orange flavored drink (10% solution); 1.0 g carbohydrate · kg^-1^ body mass) designed to elicit a low GI (GI = 37) response [2].

Following this meal the participants will be discharged and will continue recording interstitial glucose values with the CGM until the subsequent morning visits. At 180 min following the post-exercise meal (240 min post-exercise), participants will consume a low-GI bedtime snack (low fat yogurt with honey tap; GI = 38), equivalent to 0.4 g carbohydrate · kg^-1^ body mass, and will omit rapid-acting insulin. In order to improve adherence, participants will be contacted before the bedtime snack to ensure compliance, and they will be encouraged to replicate their sleeping patterns as much as possible prior to the training sessions.

The basal insulin dose after exercise will be reduced by 20% of the pre-trial basal dose. Nevertheless, the timing will be maintained throughout as per each participant’s individual regimen. Twenty-four hours afterwards, participants will return to their usual full basal insulin dose.

At 8:00 a.m. on the morning following each training assessment, participants will return to the laboratory. Here we will obtain another fasting blood sample through venipuncture and subsequently provide them with a standardized breakfast meal (sugar-coated corn flakes, peaches, semi skimmed milk; 1.0 g carbohydrate · kg^-1^ body mass). With this meal, they will self-administer their full unchanged rapid-acting insulin dose.

Following the consumption of breakfast, the participants will be discharged from the laboratory and instructed to maintain CGM for an additional 11 h (i.e., 24 h from exercise cessation). Also during this time, they will continue to monitor their diet using a food record diary and weighing their foods. We will provide the participants with a smartphone application for the recording of this information (MyFitnessPal App).

#### Control intervention: usual recommendations (sham 4-step method)

Recently, ADA published a position statement about physical activity and diabetes [16]. This statement explained how the variable glycemic responses observed in association with physical activity makes it very difficult to provide uniform recommendations for both the management of food intake and the insulin dosing regimen. Nonetheless, several instructions in this document are intended to help prevent hypoglycemia. To prevent low blood glucose level during prolonged (>30 min), predominantly aerobic exercise, additional carbohydrate intake and/or reductions in the insulin dose are typically required [12–16]. In addition to the changes in insulin regimen and carbohydrate intake, a brief (10 s) maximal intensity sprint could be performed before or after the exercise session, as suggested in the ADA guidelines, to prevent exercise-induced hypoglycemia [12]. The position statement also recommends adjusting daily basal insulin dose with reduced prandial bolus insulin and low-GI carbohydrate feeding following evening exercise for those on multiple daily injections [12]. Finally, inclusion of a bedtime snack, overnight glucose checks, or alarms and automatic pump suspension may also be warranted [16].

Patients allocated to the control group, or sham 4-step Method, will receive current usual recommendations as stated by the ADA [16], but following the scheme established with the real 4-step method (see Table 2 for the comparison for both interventions). Prior to exercise, the CGM will be installed at 7:00 a.m., and they will receive their meals in the same amount and frequency as in the real 4-step method, consisting of a breakfast at 8:00 a.m., lunch at 1:00 p.m. and pre-exercise meal at 5:00 p.m. All of the three meals will have the same caloric content as in the real intervention, and there will be no insulin modification for the first two meals. Assuming that they will be performing moderately intense physical activity later in the day, for up to 60 minutes, this group will receive a rapid-acting insulin dose that will be 75% of their usual dose concomitantly with the 5:00 p.m. meal prior to the onset of physical activity.

**Table 2 Tab2:** Scheme comparison of interventions delivered in the real and sham 4-step methods

Time		Real 4-step method	Control (sham) 4-step method
8:00 a.m.	Breakfast	Standardized cereal-based breakfast	Standardized cereal-based breakfast
	Insulin dose	Unchanged	Unchanged
1:00 p.m.	Lunch	Standardized pasta-based lunch	Standardized pasta-based lunch
	Insulin dose	Unchanged	Unchanged
5:00 p.m.	Pre-exercise meal	1 g · kg^-1^ CHO bolus	1 g · kg^-1^ CHO bolus
	Insulin dose	50% reduction	75% reduction
7:00 p.m.	Post-exercise meal	Low-GI 1 g · kg^-1^ CHO bolus	Medium-GI 1 g · kg^-1^ dinner
	Insulin dose	50% reduction	No reduction
10:00 p.m.	Snack	Low-GI 0.4 g · kg^-1^ CHO snack	Medium-GI 0.4 g · kg^-1^ CHO snack
	Insulin dose	No insulin administered	No insulin administered
Regular hour for basal insulin	Insulin dose	20% reduction	No reduction

*CHO* carbohydrates, *GI* glycemic index

One hour after finishing the exercise session, the participants will receive a carbohydrate-based meal with the same caloric content as the meal apportioned in the real interventional arm; however, we will not use low-GI food for this bolus. Contrarily we will give the participants traditional rice, tomato sauce, turkey breast, and water. With this meal we would be providing about 1.0 g of carbohydrate · kg^-1^ of body mass. We will not modify the insulin dosage administered with this meal, considering that the ADA guidelines do not suggest any specific change around this issue.

Participants will then go home where they will continue registering interstitial CGM. About 180 min after dinner (approximately 240 min after finishing the exercise session), the participants will be contacted to remind them to eat a snack before going to bed. However, this will differ from the real intervention in that this will not be a low-GI snack (200 mL of unsweetened orange juice and half a banana), and will be equivalent to 0.4 g of carbohydrate · kg^-1^ of body mass. Additionally, participants will not administer any insulin dose with this snack.

Current ADA guidelines [16] have not yet established any basal insulin dosage adjustment after intermittent exercise, and it remains for the treating physician to decide on a case-by-case basis. However, we have added a modification of 20% of the insulin dose in the interventional arm, based on results obtained from recent trials, an effect seen even with the newer basal insulin such as degludec. [5] Therefore, participants following the sham 4-step method will not receive the post-exercise modification in insulin dosage. However, in order to maintain blinding of the control group, we will provide the unchanged insulin dosage for them to administer in their own homes after the exercise session finishes, in preloaded and concealed insulin syringes, whereby they will not be able to ascertain the dose that has been served. Moreover, and with the aim of increasing adherence, the participants will be contacted through phone calls in order to remind them about eating the before-bedtime snack and to self-administer the insulin treatment provided by the trial.

At 8:00 a.m. on the morning following each training assessment, participants will return to the laboratory. Here we will obtain another fasting blood sample from them via venipuncture and subsequently provide them with a standardized breakfast meal (sugar-coated corn flakes, peaches, semi-skimmed milk). With this meal, they will self-administer their full unchanged rapid-acting insulin dose.

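### For injection users, the control's post-exercise dinner is not shown to be ADA care: the reason given for its full bolus conflicts with the ADA advice the protocol reports, and its non-low-GI content is unexplained

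*Protocol article*

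**What the plan says.** The Intervention section describes the control as "following the recently published ADA usual recommendations of care [12–16] before, during and after exercise (sham 4-step method". The Control intervention section repeats the label: control participants "will receive current usual recommendations as stated by the ADA [16", delivered within the timing scheme of the real method and set out in Table 2.

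That section first summarises the ADA position statement. For evening exercise it says that the statement "recommends adjusting daily basal insulin dose with reduced prandial bolus insulin and low-GI carbohydrate feeding following evening exercise for those on multiple daily injections". A separate sentence covers the night: "Finally, inclusion of a bedtime snack, overnight glucose checks, or alarms and automatic pump suspension may also be warranted [16".

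It then describes the control's dinner: "One hour after finishing the exercise session, the participants will receive a carbohydrate-based meal" with the same caloric content as in the active arm; "however, we will not use low-GI food for this bolus". The insulin given with it is not modified, "considering that the ADA guidelines do not suggest any specific change around this issue". Table 2 shows this meal as medium-GI with no reduction of the bolus. The active arm has a low-GI meal with a 50% reduction.

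Basal insulin is handled apart. The section says that the ADA has set no adjustment "after intermittent exercise, and it remains for the treating physician to decide on a case-by-case basis", and the control's basal dose is left unchanged.

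**The concern.** The control section summarises ADA advice and then defines a control meal that does not follow that summary. On the bolus, it says in one place that the ADA recommends a reduction after evening exercise for injection users, and in another that the ADA suggests no specific change. On the glycemic index, it reports advice for low-GI feeding, then chooses a meal that is not low-GI and gives no reason.

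This concerns the comparator for the primary safety outcome. The Abstract, the last paragraph of the Background and the Intervention section name that comparator as ADA care, and the objective restated under Randomization names it as guideline care. If the control departs from that care at a meal shortly after exercise, a lower event rate under the 4-step method may partly reflect the departure. The safety hypothesis stated before the cognitive tests, of the same or fewer events, is equally relative to the named comparator, so the point does not depend on a formal superiority claim.

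**Working it through.** The protocol gives no figure for this point, so the check is mainly a comparison of statements.

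**1. Does the reported advice apply to trial participants?** Table 1 excludes regimens other than pump infusion or multiple daily injections, so injection users are eligible. The Active intervention section has participants arrive at 5:00 p.m. for an evening session. The reported advice is for injection users after evening exercise, so it applies to them. No such advice on the bolus or meal is reported for pump users.

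**2. Dinner bolus.**
- ADA advice as summarised: reduced prandial bolus.
- ADA advice as given in the reason for the control dose: no specific change.
- Control regimen (Table 2): no reduction.

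These are two accounts of the same advice, and they conflict.

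**3. Dinner glycemic index.**
- ADA advice as summarised: low-GI feeding.
- ADA advice as given where the control meal is described: none stated.
- Control regimen (text and Table 2): not low-GI, medium-GI.

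Here there is only one account of the advice. The fault is an unexplained departure from it under an ADA label.

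**4. Which account of the bolus is right?** The documents cannot say. The sentence with the recommendation attributes it to the position statement, which the section introduces as reference [16], but cites [12]. The guideline itself is not at hand.

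**5. Size of the contrast at this meal.** Carbohydrate is 1 g per kg in both arms. The dinner bolus is 100% of the usual dose in the control and 100% − 50% = 50% in the active arm. The ratio is 100 / 50 = 2.0.

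**6. Position in the outcome window.** The primary outcome counts participants with a confirmed episode in the 24 h after the session. The text places dinner 1 h after exercise, so 24 − 1 = 23 h follow it, and 23 / 24 = 95.8%. This shows only that the meal falls early in the window. It does not measure an effect.

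**7. What cannot be computed.** The effect of either dinner item on event rates, and the share of participants on injections, do not follow from the documents.

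**The case against.** **The phrase about no specific change may mean only that the ADA gives no dose size.** The section does say that uniform recommendations are very difficult, and the reported advice gives a direction without a percentage. This reading is plausible and softens the conflict. It does not remove it, because a fixed zero reduction is still not a reduced bolus. Nor does it explain the meal's glycemic index.

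**The regimen is fully disclosed.** This stands. Table 2 shows every dose and meal, the comparator is repeatedly called a sham 4-step method, and the Blinding section describes ADA recommendations masked in that scheme. A contrasting comparator is also a legitimate choice. But the full bolus is justified by ADA silence, not by contrast. The Abstract, the Background hypothesis and the objective under Randomization carry no sham qualifier. The fault lies in the label and the stated reason.

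**Basal insulin has the same kind of reason, so it should be treated alike.** There is a similar tension, since the reported advice also mentions adjusting the basal dose. The reason given for basal is, however, limited to intermittent exercise and leaves the decision to the treating physician. The reason given for the bolus has no such limit. Basal is therefore not counted here. The snack's glycemic index is not counted either, because the reported advice on a bedtime snack specifies none.

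**A reader might infer that the control has been shown to be non-ADA care.** The documents do not support that. If the reason given for the bolus is the correct account, the bolus is consistent with the guideline and the summary sentence is what needs correcting. Nor do they support a claim that the section contradicts itself about ADA advice on glycemic index, since it states that advice only once.

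**Conclusion.** The point holds for participants on multiple daily injections and for the post-exercise dinner. The reason given for the unreduced bolus conflicts with the protocol's own report of ADA advice, and the choice of a meal that is not low-GI has no stated reason. The ADA label is therefore not established for that meal.

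The consequence is conditional. If the reported recommendation is right, fewer hypoglycemic events under the 4-step method could reflect a control given twice the active arm's dinner bolus, without the low-GI component, and so departing from ADA care. If the statement of no specific change is right, the bolus can keep its label, but the dinner's glycemic index still has to be checked. A reader might go further and conclude that a favourable result can never be read as a benefit over ADA care. That would need the guideline text, which the documents do not provide.

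The conclusion assumes that the two dinner rows of Table 2 describe what will be given. It does not extend to pump users and claims no particular effect on event rates. It should be fixed, because it determines what the primary safety comparison may be said to show.

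**What to change.** Before enrolment (Trial status lists recruitment as pending):

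1. Check the two dinner rows of Table 2, meal and insulin, against the cited guideline for injection users after evening exercise, with clinical sign-off.
2. Correct whichever is wrong: the summary of the recommendation, or the reason given for the control's bolus. Correct the citation with it.
3. Unless both rows are shown to match the guideline, name the comparator as the fixed sham regimen of Table 2 in the Abstract (Methods/design), the last paragraph of the Background, the Intervention section, the objective under Randomization, and the trial's conclusion. State that benefit over ADA-recommended post-exercise care is not tested for injection users.

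No dose is proposed here. The cost is one source check and wording in four places plus the conclusion. The downside is a narrower claim.

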The effect that the modifications on blood glucose levels before, during, and after exercise have on the performance of athletes in this type of sport has not been accurately established, and evidence addressing this hypothesis is scarce [1]. To our knowledge there is only one study [8] in adolescents with T1D that found that hypoglycemia, but not hyperglycemia, impaired both the patients’ sports performance (tennis, basketball, or soccer skills) and their cognitive function. However, this trial had some important limitations including the fact that the sport performance tests were of a relatively short duration and did not demonstrate how blood glucose levels affected mental and physical stamina [12].

Campbell et al. [2] developed a 4-step method that succeeded in protecting participants with T1D from both hypoglycemia and hyperglycemia throughout exercise periods and the 24-h interval following exercise sessions [2]. This method includes the following interventions: (1) 75% reduction of pre-exercise rapid-acting insulin dose (or 50% if intermittent exercise) given before a meal containing 1 g carbohydrate · kg^-1^ 60 min prior to physical activity [13]; (2) post-exercise meal containing 1 g low-glycemic index (GI) carbohydrate · kg^-1^ 60 min after physical activity with 50% reduction on rapid-acting insulin dose [14]; (3) consumption of a bedtime snack containing 0.3 g carbohydrate · kg^-1^ also with a low GI and omitting prandial insulin administration for this meal [15]; and (4) 20% reduction of basal insulin across the day when physical activity is performed [2].

In clinical trials, this 4-step method has demonstrated that it is possible to optimize blood glucose level during and after exercise by making mealtime adjustments to both rapid-acting and basal insulin, and to pre-exercise and post-exercise carbohydrate composition [2]. However, previous clinical trials have focused on evaluating patients’ performance in continuous forms of sports like running or cycling, whereas evidence supporting this 4-step strategy in intermittent activities such as soccer, tennis, and basketball, is still lacking.

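### The control arm's pre-exercise insulin dose is 75% of usual in the text but a 75% reduction in Table 2, which reverses the direction of the contrast with the active arm

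*Protocol article*

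**What the plan says.** **Control arm, text.** In the section on the control intervention, the 5:00 p.m. dose is described as follows: "this group will receive a rapid-acting insulin dose that will be 75% of their usual dose concomitantly with the 5:00 p.m. meal". The stated basis is moderately intense activity of up to 60 minutes later in the day. The same paragraph sends the reader to Table 2 for the comparison of the two interventions.

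**Control arm, table.** In Table 2, the insulin row for the 5:00 p.m. pre-exercise meal shows a 50% reduction for the real 4-step method and a 75% reduction for the control.

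**Active arm.** The Intervention section gives "a meal 60 min pre-exercise, with 50% of insulin dose". The section on the real 4-step method says "they will self-administer a 50% reduced pre-meal rapid-acting insulin dose into the abdomen". Table 2 shows a 50% reduction. All three mean half of the usual dose.

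**Guideline basis for the control.** The Intervention section says only this: "The ADA guidelines suggest that short-acting insulin is reduced depending on the mean exercise intensity in both exercise modes". It gives no percentage.

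**The concern.** The text states the dose that is given and the table states the dose that is taken away, and both use the figure 75. At 50% the two ways of writing mean the same dose, which is why the active arm shows no conflict. At 75% they do not.

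The comparator's insulin dose is therefore undefined, and so is the direction of the planned difference at the first step of the method. The Discussion credits that step with protecting against hypoglycemia during and soon after exercise. Under the text, the active arm gets the deeper cut, as that purpose suggests. Under the table, the control arm does.

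The dose is taken about an hour before the soccer tests, which the article lists as secondary outcomes, and before the Stroop test that follows each session. It also acts on pre-exercise glucose. The Research aim seeks an optimal level of pre-exercise glucose, and the Statistical methods correlate the test scores with it.

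**Working it through.** **Inputs**
- Control, text (control intervention section): 75% of the usual dose given.
- Control, Table 2 (5:00 p.m. insulin row): 75% reduction.
- Active (Intervention section, real 4-step section, Table 2): 50% given, or 50% reduction.

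**Formulas**
- Dose given = 100% − reduction.
- Contrast = control dose given − active dose given.

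**Step 1: active arm.** A 50% reduction gives 100 − 50 = 50% of usual. This matches the wording that 50% of the dose is given, so the active arm is consistent.

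**Step 2: control arm.** The table's 75% reduction gives 100 − 75 = 25% of usual. The text's figure is 75% of usual, so the table does not reproduce it. The ratio is 75/25 = 3 and the difference is 75 − 25 = 50 percentage points of a usual dose.

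**Step 3: contrast between arms.**

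| Reading | Control given | Active given | Control − active | Control / active |
|---|---|---|---|---|
| Text | 75% | 50% | +25 points | 1.5 |
| Table 2 | 25% | 50% | −25 points | 0.5 |

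The contrast has the same size and the opposite sign.

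**Step 4: is the table unreliable in general?** The control column of Table 2 was compared with the text, row by row.

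| Insulin row | Table 2, control | Text, control | Result |
|---|---|---|---|
| Breakfast | Unchanged | "there will be no insulin modification for the first two meals" | Agrees |
| Lunch | Unchanged | Same sentence | Agrees |
| Pre-exercise, 5:00 p.m. | 75% reduction | 75% of usual given | Conflicts |
| Post-exercise | No reduction | "We will not modify the insulin dosage administered with this meal" | Agrees |
| Snack | None given | "participants will not administer any insulin dose with this snack" | Agrees |
| Basal | No reduction | Unchanged dose supplied | Agrees |

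Five of the six rows agree and one conflicts. The row in question is complete, with one value per arm in the expected column, so a broken table does not explain the conflict.

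**Step 5: what else differs before exercise?** Breakfast, lunch and the 5:00 p.m. meal have the same caloric content in both arms, and insulin for the first two is unchanged in both. The sections on the two interventions place the basal change after exercise. The 5:00 p.m. dose is then the only planned difference between arms before the soccer session.

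**Step 6: who is exposed?** In the crossover each participant has one control session. The target is 28 participants, which includes the 15% dropout allowance on 24.

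**The case against.** The strongest reply is that the text is probably right and the table cell is a slip. The text is a full sentence with a meal, a time and a reason, whereas Table 2 is a summary. At the other two insulin doses that differ between arms (post-exercise and basal), control gets more insulin than active, and only the text's reading fits that pattern. The Background also describes the method with a "75% reduction of pre-exercise rapid-acting insulin dose (or 50% if intermittent exercise" alternative, and its 75% figure could have been copied into the wrong cell. This makes the text the likelier reading, but it is inference. The Background sentence describes the 4-step method and not the control, and no other statement fixes the control dose.

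A second reply concerns basal insulin. The Background describes the 20% basal cut as running across the exercise day, basal timing follows each participant's own regimen, and pump users are eligible. For some participants part of the basal difference might fall before the session. The sections that define the trial's regimens nevertheless place the change after exercise. On any reading, the 5:00 p.m. dose is the only difference in meals or rapid-acting insulin before the session.

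A third reply is that the outcomes most exposed are not primary. The Research aim treats the comparison of soccer skills as exploratory, and the cognitive tests are called both exploratory and secondary. The primary outcome covers the 24 h after the session, and its post-exercise and basal contrasts do not change. This is correct, and it limits the consequence for the primary result.

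Finally, dosing instructions outside the article may carry a single value, and no misdosing is shown. That is possible, but the article states the dose twice with two values, so this is a contradiction and not a detail left to a fuller document.

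**Conclusion.** The concern holds. The control arm's pre-exercise rapid-acting dose is stated as 75% of usual in one place and, in effect, 25% of usual in another. That is a threefold difference, and it turns a contrast of +25 points against the active arm into −25 points. It must be fixed, because it leaves open both a comparator insulin dose in a safety trial and the direction of the first step of the intervention.

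The arithmetic needs no outside assumption. The statement that this is the only planned difference before exercise rests on the basal change coming after exercise, as the intervention sections say. The contradiction does not affect the sample size calculation, and its effect on the primary outcome is limited. Both readings reduce the usual dose. The text may be the likelier reading, but the article does not establish it.

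**What to change.** Before first enrolment (recruitment is listed as pending), the investigators should confirm the intended control dose. The control intervention section and the Table 2 cell should then give it in the same form, as a percentage of the usual dose given.

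- If the text is right, the Table 2 cell should read: 25% reduction (75% of usual dose given).
- If the table is right, the sentence in the text should say 25% of the usual dose.

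The cost is one table cell or one sentence, with submission to the review board as the Ethical considerations section requires for relevant changes. No extra patients, visits or procedures are needed.
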